### Analysis of immunogenicity

**Growth Inhibition Assays (GIA)**

Growth inhibition assays (GIA) will be reported in a tabular manner as the percent growth inhibition seen at a given serum dilution compared with the same dilution of pre-immune serum from the same volunteer. GIA will be performed in all volunteers pre- and post-vaccination following standard procedures. An individual serum will be considered to be GIA positive, if compared with paired pre-immune control serum, the growth inhibition value is greater than 20%.

The criteria for FMP010/AS01B progression to Phase 2b and future development are based on establishing statistically significant differences in the ability of the FMP010/AS01B and FMP1/AS02A vaccines to induce biologically relevant antibody responses against homologous parasites *in vitro*. FMP010/AS01B should induce inhibitory antibody responses above the established cutoff level, 20% inhibition (20% serum pLDH GIA assay) in a minimum number of volunteers against homologous parasites, *P. falciparum* FVO (i.e. 10 out 15, thus 67% seropositivity).

| **Criteria** | **FMP010/AS01B** | **FMP1.AS02A** |
| --- | --- | --- |
| Seropositivity | 10 out of 15, 67% | 2 out of 5, 40% |
| Mean Inhibition (%)  Homologous parasites | 30 ± 5 | 15 ± 3 |

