Although MSP1-based vaccines such as the 3D7 allele have been tested previously in humans, this is the first time that this candidate antigen (FMP010) based upon the FVO allele will be administered in humans. Therefore, a dose-escalation approach (1/5th dose of 10 micrograms and a full dose of 50 micrograms) will be taken to evaluate safety and reactogenicity in healthy malaria-naïve individuals in the U.S. Safety will be assessed after the first 1/5th dose has been given prior to proceeding to the full dose. Safety of the full dose in adults in the U.S. will be assessed after two vaccinations prior to proceeding to administration of the full dose in malaria-experienced healthy adults in Western Kenya. The candidate vaccine, FMP010/AS01B, consists of the FMP010 antigen formulated with GSK proprietary adjuvant AS01B, the adjuvant currently considered for use in planned pediatric Phase 3 malaria vaccine trials with the pre-erythrocytic malaria candidate vaccine, RTS,S/ASO1B.

Prior experience with MSP1-based vaccines in humans has indicated the requirement for potent adjuvants to elicit sufficiently high antibody titers against epitopes within the carboxy-terminal region of MSP1. Pre-clinical immunogenicity studies in small animals indicate that the FVO allele of the MSP1 antigen is superior to the 3D7 allelic variant in producing functional anti-parasite antibody activity as assessed in the in vitro growth inhibition assay (GIA).

A previous Phase 1/2b pediatric malaria vaccine study conducted in Kenya with the 3D7 allele of MSP1 (FMP1) in the adjuvant AS02A did not adequately demonstrate protective efficacy against clinical disease (manuscript in preparation). However, the 3D7 allele is rare at this location. Most adults in the target study population already have some level of pre-existing immune response to this antigen, therefore data from this population will be required to make an accurate assessment of the immunogenicity of the vaccine.

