### FMP1/AS02A

The FMP1 antigen has been under clinical development at WRAIR (30) for over 10 years with accumulated safety and reactogenicity data from two trials conducted at WRAIR and four trials in endemic areas in Mali and Kenya. A Phase 1 dose-escalation study of FMP1/AS02A in 15 malaria-naïve adults conducted at WRAIR in 2001 demonstrated all dose levels to be safe and well tolerated, with no grade 3 adverse reactions and no serious adverse events (31). The vaccine was immunogenic with seroconversion in all vaccinees after the second vaccination. The antibodies induced by this vaccine also demonstrated homologous GIA activity of approximately 15% in 2 of 5 volunteers receiving 50 µg of FMP1 in ASO2A, while there was no demonstrable activity against heterologous (FVO) parasites. Also seen was circumferential staining of fixed schizonts by IFA. A Phase 1/2a study conducted at WRAIR with FMP1/AS02A and RTS,S/AS02A demonstrated that FMP1/AS02A was safe and immunogenic, although it did not confer protection (personal communication [name]).

Of Phase 1 studies conducted in malaria-endemic areas, the first was performed in forty adult participants in Kombewa, Kenya in 2002 comparing FMP1/AS02A to rabies vaccine (32). The most common local side effect related to vaccination with FMP1 was pain which resolved within 48 hrs. No Grade 3 systemic reactions and no vaccine-related vaccine SAE occurred in either group. In adults in Mali, a 50 μg dose of FMP1 in AS02A was safe and well-tolerated with Grade 3 swelling being the most common local side effect as compared to rabies vaccine (33). This swelling lasted less than 48 hours and often was unnoticed by the volunteers.

In Kombewa, Kenya, a Phase I dose-escalation trial of FMP1/AS02A and a rabies comparator vaccine *Imovax*® in children 12-47 months of age was completed in 2003-2004 (33). Safety data showed that the most common solicited adverse events were pain and swelling at the injection site occurring in greater frequency in children who received FMP1/AS02A. These local symptoms had the highest incidence after the first vaccination and resolved within 48-72 hours. Grade 3 local symptoms occurred in less than 10% of children in all dose cohorts. The commonest general symptoms were fever and irritability and these also resolved within 24-48 hours.

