# Secondary Objective

Measure and compare, by Growth Inhibition Assay (GIA), the functional humoral immune responses induced in malaria experienced adults in Kenya to that induced in healthy malaria-naïve adults from the US by FMP010/AS01B and FMP1/AS02 A.

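### The Kenyan GIA analysis names no comparison with the randomised rabies arm, so inhibition acquired after Day 0 from other causes can be credited to the vaccine

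*Protocol*

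**What the plan says.** Section 10.4.3 (Growth Inhibition Assays) sets the reference for each result: growth inhibition is "compared with the same dilution of pre-immune serum from the same volunteer". A serum counts as positive "if compared with paired pre-immune control serum, the growth inhibition value is greater than 20" percent. The same section states that "GIA will be performed in all volunteers pre- and post-vaccination following standard procedures", so rabies recipients are assayed too.

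The comparisons are set in three places:
- The secondary objective in section 10.1, repeated in the Synopsis, compares Kenyan adults with malaria-naive "adults from the US by FMP010/AS01B and FMP1/AS02 A". Section 2.1 gives the Kenya-US comparison without FMP1/AS02A.
- Section 1.3.4 says that the FMP1/AS02A responses come from an earlier vaccine trial.
- Section 10.4.3 bases progression to Phase 2b on "statistically significant differences in the ability of the FMP010/AS01B and FMP1/AS02A vaccines to induce biologically relevant antibody responses", together with a minimum count against FVO parasites of "10 out 15, thus 67% seropositivity".

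Part B randomises 20 volunteers (minimum 16) to FMP010/AS01B and 10 (minimum 8) to rabies vaccine (section 5.3, Study Design). None of the GIA comparisons above names the rabies group.

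**The concern.** Part B follows malaria-experienced adults in an endemic area from Day 0 to Day 70 (14 days after dose 3) and Day 112. The Synopsis rationale says: "Most adults in the target study population already have some level of pre-existing immune response to this antigen". It also expects natural infection, ideally, to recall and raise the response that vaccination primes. A rise above 20% from Day 0 could therefore reflect an infection during follow-up, antimalarial drug carried in the serum, or drift between assay runs. Group 4 shares all of these and Group 3 minus Group 4 would cancel them on average, whereas neither stated comparator shares the Kenyan exposure.

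At stake is the interpretation of Kenyan GIA positivity and of the secondary objective. If the progression count is taken in Kenya, the decision to move to Phase 2b is affected as well.

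**Working it through.** **1. What each stated comparison removes.**
- *Own pre-immune serum:* removes inhibition present at Day 0, but not changes after Day 0 from other causes.
- *Kenya v US adults:* same product, but population, prior immunity and exposure during follow-up all differ.
- *FMP010/AS01B v FMP1/AS02A:* differs in antigen, adjuvant and trial. The benchmark in section 1.3.3 is "homologous GIA activity of approximately 15% in 2 of 5 volunteers" who received 50 µg, in a study of malaria-naive adults. About 15% lies below the 20% cutoff used in section 10.4.3, another reason to read this comparison descriptively.
- *Group 3 v Group 4:* same place, period, exposure and assay, and randomised. It is not specified for GIA.

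**2. The protocol's own figures.** 10/15 = 66.7% and 2/5 = 40.0%, as stated. Fisher's exact test on 10/15 v 2/5 gives p = 0.35 two-sided, so meeting the count would not by itself show a significant difference in positivity from the historical group.

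**3. Illustration of the bias.** Assumptions: v is the share converted by the vaccine; q is the share that would turn positive without it after Day 0; the two are independent; the 10-of-15 rule is applied to Kenyan vaccinees. The documents give neither v nor q.

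Observed rate p = 1 − (1 − v)(1 − q). Chance of passing = P(X ≥ 10), X ~ Binomial(15, p).

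| v | q | p | P(X ≥ 10 of 15) |
|---|---|---|---|
| 50% | 0% | 50% | 15% |
| 50% | 5% | 52.5% | 20% |
| 50% | 20% | 60% | 40% |
| 50% | 30% | 65% | 56% |
| 40% | 0% | 40% | 3% |
| 40% | 20% | 52% | 19% |
| 40% | 30% | 58% | 34% |

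With no vaccine effect (v = 0), the chance of passing is 0.4% at q = 30% and 3% at q = 40%. Background conversion inflates a modest vaccine effect; it rarely creates a pass on its own.

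**4. What the randomised contrast can deliver.** The protocol states no alpha, so two-sided 5% is assumed.
- Mean paired inhibition, two-sample t test, 20 v 10: the standard error is SD × √(1/20 + 1/10) = 0.387 SD, and 80% power needs a difference of 1.12 SD (noncentral t, 28 degrees of freedom).
- Proportion positive, 67% in Group 3, Fisher's exact test: power for 20 v 10 (16 v 8) is 0.83 (0.74) if 10% of Group 4 turn positive, 0.58 (0.52) at 20% and 0.37 (0.32) at 30%.

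The contrast has useful power only if background conversion is uncommon; otherwise it serves as an estimate with an interval.

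**The case against.** The strongest reply is that a by-arm analysis is already implied and only its detail is missing. GIA is run in all volunteers, section 10.3 analyses the total cohort by treatment received and refers to a differential treatment effect on immunogenicity, and the sample size section promises comparative statistics between groups with low power. That stands to this extent: nothing forbids the contrast, and Group 4 values should exist. A reader might infer that the rabies arm is shut out of the GIA analysis, but the text supports only that no GIA contrast with it is specified. The reply does not dispose of the point, because the protocol itself fixes the reference, the comparisons and the progression criteria, and gives the rabies arm no part in them. The one named immunogenicity test, the Day 70 t test on ELISA titres, looks for a dose response, and Part B has a single dose of the candidate vaccine.

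A second reply is that the paired reference already deals with natural immunity. It does for immunity present at Day 0, which is what the Synopsis statement on pre-existing response describes. A reader might infer that naturally acquired immunity as a whole is counted as vaccine response; only what arises after Day 0 can be.

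Third, the Kenya-US and FMP1/AS02A comparisons are the stated scientific question, and the protocol does not claim that they identify a randomised effect. That is fair, and they should be kept. They cannot, however, show how much of the Kenyan response the vaccine induced.

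**Conclusion.** The point holds in limited form. As specified, Kenyan GIA positivity and the Kenya-US contrast can credit the vaccine with boosting, drug in serum or assay drift after Day 0, although a concurrent randomised control is assayed that could separate them. The size cannot be stated from the documents. The illustrative rise from 15% to 20, 40 or 56% rests on an assumed 50% vaccine conversion, independent background conversion of 5, 20 or 30%, and use of the rule in Kenya.

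A reader might go further and conclude that the Phase 2b progression rule is itself distorted by natural exposure. The documents do not support that. Section 10.4.3 does not say whose 15 volunteers are counted; 15 matches neither Group 3's planned 20 nor its minimum of 16, and Part A enrols 26 US volunteers. If the 15 are US adults, the rule is unaffected.

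**What to change.** In section 10.4.3:
- Name Group 3 minus Group 4 at Day 70 as the main estimate of vaccine-induced GIA in Kenya: the difference in mean paired percent inhibition (FVO first, then 3D7) and the difference in proportion GIA-positive, each with a 95% confidence interval. Acknowledge the low power.
- Keep the US and FMP1/AS02A comparisons, labelled descriptive.
- State which group the 10-of-15 rule applies to. If it is Kenyan, report it beside Group 4 positivity.
- Treat any analysis by HRP-2/pLDH status as supportive only, where results exist, and label it as conditioning on post-randomisation events. These assays are exploratory and depend on remaining sample (sections 2.2 and 10.2). Section 7 does not name antimalarials among the drugs that must be entered in the CRF, so a split by treatment is not assured either.

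The cost is mainly wording; no extra volunteers, visits or blood are needed. One confirmation is required: section 10.2 also lists Kenyan GIA among assays done if sample remains, and the serology plan lets researchers test fewer time points. The protocol should therefore commit to Day 0 and Day 70 GIA in both arms.

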### Study Design

This trial will be conducted in two parts. Part A will be conducted in the US at WRAIR and Part B in at the Walter Reed Project/KEMRI in Kisumu, Kenya. A total of 56 volunteers will be enrolled with 26 enrolling in part A and 30 in part B. For Part B, 20 volunteers (minimum 16) will be enrolled to receive FMP010 at 50 µg in AS01B (Group 3) and 10 (minimum 8) volunteers enrolled to receive a comparator rabies vaccine Rabipur (Group 4). This part will be randomized and blinded.

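### Section 10.4.3 bases Phase 2b progression on significant differences from FMP1/AS02A, but its responder mark of 10/15 against the printed 2/5 gives p = 0.35, the deciding endpoint is not named, and the 2/5 does not fit the protocol's own cutoff

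*Protocol*

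**What the plan says.** The progression rule is in Protocol Section 10.4.3, under Growth Inhibition Assays.

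- The criteria for "FMP010/AS01B progression to Phase 2b and future development are based on establishing statistically significant differences" between FMP010/AS01B and FMP1/AS02A. The property compared is the ability to "induce biologically relevant antibody responses against homologous parasites".
- The next sentence sets a minimum number of volunteers above the 20% inhibition cutoff against FVO parasites: "10 out 15, thus 67% seropositivity".
- The criteria table has two rows. The seropositivity row reads "10 out of 15, 67% | 2 out of 5, 40" per cent. The mean homologous inhibition row gives 30 ± 5 for FMP010/AS01B and 15 ± 3 for FMP1/AS02A.
- A serum counts as positive if, against its paired pre-immune control, "the growth inhibition value is greater than 20" per cent.

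Two other places bear on these figures. Section 1.3.3 describes the Phase 1 result for FMP1/AS02A as "homologous GIA activity of approximately 15% in 2 of 5 volunteers" at the 50 µg dose. The Study Design part of Section 5.3 says that "20 volunteers (minimum 16) will be enrolled to receive FMP010" in Part B.

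**The concern.** This is the protocol's stated rule for taking the vaccine to Phase 2b. The significance sentence, the minimum count and the FMP1/AS02A comparator stand together, so a reader expects the count to have something to do with significance against that comparator. On the responder row it does not.

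The table offers a second row that could carry the requirement, but the text does not say whether one row or both must be significant. If the result lands at or just above the minimum count, the reading could then be chosen after the data are seen.

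The comparator adds to the problem. The 2/5 appears to count volunteers whom the paragraph's own positivity rule would score as negative.

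**Working it through.** **Inputs.** 10/15, 2/5, 30 ± 5, 15 ± 3 and the cutoff of more than 20% come from Section 10.4.3. About 15% inhibition in 2 of 5 comes from Section 1.3.3. Group 3 size, 20 (minimum 16), comes from Section 5.3. The protocol states neither alpha nor sidedness; I assume 0.05, two-sided.

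**Printed percentages.** 10/15 = 66.7% and 2/5 = 40.0%. Both reproduce.

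**Responder row, 10/15 against 2/5.** Of 20 subjects, 12 are responders and 15 are in the FMP010 group. With X the FMP010 responders and margins fixed, P(X = k) = C(12,k)·C(8,15−k)/C(20,15), and C(20,15) = 15,504.

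- P(10) = 66·56/15,504 = 0.2384
- P(11) = 12·70/15,504 = 0.0542
- P(12) = 1·56/15,504 = 0.0036
- One-sided p = 0.296
- In the other tail only P(7) = 792/15,504 = 0.0511 is no larger than P(10), so two-sided p = 0.296 + 0.051 = **0.347**

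Other two-sample tests agree: chi-square 0.292 (0.598 with continuity correction), Barnard 0.375, Boschloo 0.361. The row comes near significance only if 40% is treated as a known constant (exact one-sided 0.034, two-sided 0.061), but 40% is an estimate from five people.

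**How far the count is from significance, with 2/5 at face value.** Fisher two-sided: 13/15 p = 0.073, 14/15 p = 0.032. If the true response rate is 2/3, P(at least 10 of 15) = 0.62 and P(at least 14 of 15) = 0.019.

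**Mean inhibition row, 30 ± 5 against 15 ± 3, taking n = 15 and n = 5.**

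| Reading of ± | Test | Standard error of difference | t | p |
|---|---|---|---|---|
| SD | Welch | √(25/15 + 9/5) = 1.86 | 8.06 | < 0.00001 |
| SD | pooled | √[(14·25 + 4·9)/18]·√(1/15 + 1/5) = 2.39 | 6.27 | < 0.00001 |
| SE | Welch | √(25 + 9) = 5.83 | 2.57 | 0.019 |
| SE | pooled | √[(14·375 + 4·45)/18]·√(1/15 + 1/5) = 8.97 | 1.67 | 0.11 |

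At its printed values this row is significant on three of the four readings.

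**The benchmark under the protocol's own cutoff.** About 15% is below 20%. If the two volunteers in Section 1.3.3 are the 2 in the table, the rule scores them negative and the benchmark is 0/5. For 10/15 against 0/5, P(10) = C(10,10)·C(10,5)/15,504 = 252/15,504 = 0.0163. The opposite extreme, P(5), is equal, so two-sided p = **0.033**. One choice about the comparator moves the same count from p = 0.35 to p = 0.033.

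**Denominator.** The smallest counts of at least 66.7% are 14/20 (70%; 13/20 is 65%) and 11/16 (69%; 10/16 is 62.5%). Against 2/5 they give p = 0.31 and p = 0.33, so the larger group does not change the result.

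**The case against.** The strongest reply is that the significance sentence is not tied to the responder row. It concerns the ability to induce relevant antibody responses, and the same table prints a mean inhibition row that is significant on most readings. This stands. A reader might infer that a 10/15 result necessarily fails the stated criterion. The protocol does not support that, because such a trial could still show a significant difference in mean inhibition.

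Second, a minimum is a floor. The floor and the significance requirement may be two conditions that must both hold, in which case 10/15 without significance is simply a no-go. That reading is coherent, but the text does not state it, nor which row would have to be significant.

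Third, the p-value of 0.35 takes 2/5 at face value, and the protocol itself casts doubt on it. This also stands. A reader might infer that 14/15, or 15/16 or 18/20 at the Group 3 sizes, should replace the printed count. Those figures depend on the doubtful benchmark.

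Fourth, Section 10.4.3 does not say that the 15 are Group 3. Part A enrols 26 and its group sizes are not given here. Section 10.2 lists growth inhibition in Kenyan adults among the exploratory endpoints as well as having growth inhibition as the secondary endpoint. So 15 cannot be called an error for Group 3; its population is unstated.

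Finally, the sample size section concedes low power, and test and alpha may properly be left to a statistical analysis plan. I do not count their absence. But the protocol itself fixes the criterion, count and comparator, and those need to agree.

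**Conclusion.** The point holds as a defect in a decision rule. The responder criterion does not have the significance on which the paragraph says its criteria are based: 10/15 against the printed 2/5 gives p = 0.35, and no two-sample test tried makes it significant. The rule does not name the endpoint that must be significant, so a result at the minimum count can be read either way. The comparator conflicts with the protocol's positivity rule, and resolving that conflict could reverse the responder result (p = 0.033 at 0/5). The count is set on 15 without a stated population, while Group 3 has 20 (minimum 16).

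This rests on a two-sided 0.05 level, on the two FMP1/AS02A volunteers in Section 1.3.3 being those in the table, and, for the mean row, on group sizes of 15 and 5. The protocol states none of these. The change should be made before data are available. It bears on the Phase 2b decision and not on participant safety.

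**What to change.** Revise the growth inhibition paragraph and table in Section 10.4.3:

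1. State the 67% responder rate as a fixed minimum, reported with its exact 95% confidence interval (10/15: 38–88%; 14/20: 46–88%). Say that it does not by itself establish a significant difference from the printed 2/5.
2. Attach the significance requirement to one named endpoint. Percent inhibition on its continuous scale is the natural choice. Define ± as SD or SE.
3. Re-score the FMP1/AS02A benchmark with the more-than-20% cutoff, or correct the 15% or the 2/5 figure, before any comparison is made.
4. State which population the 15 refers to. If it is Group 3, give the count for 20 (14/20) and for the minimum of 16 (11/16).

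Do not write 14/15, 15/16 or 18/20 into the rule until the benchmark is reconciled.

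The cost is the wording of one paragraph and one table. The downside is a less favourable stated claim, since the responder count would no longer be presented alongside a claim of significance.

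### The Phase 2b progression criterion scores FMP1/AS02A as 2/5 positive against its own 20% cutoff, and its 10/15 target names no group and matches none described for Part B

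*Protocol*

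**What the plan says.** All of the following is in the protocol.

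- **Positivity rule** (section 10.4.3, Growth Inhibition Assays): an individual serum is positive if, against its paired pre-immune serum, "the growth inhibition value is greater than 20" percent.
- **Basis of progression** (same section): the criteria for Phase 2b are "based on establishing statistically significant differences in the ability of the FMP010/AS01B and FMP1/AS02A vaccines" to induce relevant antibody responses against homologous parasites. No test or significance level is given there.
- **Target** (same section): FMP010/AS01B should exceed the cutoff in a minimum number of volunteers, given as "10 out 15, thus 67% seropositivity".
- **Criteria table** (same section): the seropositivity row reads "10 out of 15, 67% | 2 out of 5, 40" percent. The mean homologous inhibition row sets 30 ± 5 for FMP010/AS01B beside 15 ± 3 for FMP1/AS02A. The meaning of ± is not stated.
- **Source of the FMP1 figures** (section 1.3.3): antibodies induced by that vaccine "also demonstrated homologous GIA activity of approximately 15% in 2 of 5 volunteers" receiving the 50 µg dose.
- **Size of the FMP010 arm in Part B** (section 5.3, Study Design): "20 volunteers (minimum 16) will be enrolled to receive FMP010". Part A enrols 26 volunteers; their split between Groups 1 and 2 is not given in this document.

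**The concern.** The criterion uses one definition of a positive serum for the new vaccine and, it appears, another for the comparator. If two volunteers at about 15% count as positive for FMP1/AS02A, a cutoff of 20% has not been applied to them. The comparator count then determines whether the target meets the stated basis of a significant difference.

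The target also carries both a count and a percentage, and these agree only when the denominator is 15. No Part B group of 15 is described, and 15 is below Group 3's stated minimum of 16.

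This is the protocol's only stated rule for moving the vaccine to Phase 2b. Two people applying it to the same data could reach opposite decisions, and the choice between readings would be made after the results were known.

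**Working it through.** **Assumptions.** Significance level 0.05, since the criterion states none. Group 3 is used for the n = 20 and n = 16 calculations, as the only FMP010 group described for Part B.

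**1. Reproduce the stated percentages.** 10/15 = 66.7% and 2/5 = 40.0%. Both are correct divisions; the problem is what is counted.

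**2. Apply the cutoff to the comparator.** Two volunteers at about 15%, rule > 20%: neither is positive, so the count is 0/5 on the protocol's figures. The table's own mean bears on this too. With five values of mean 15, two of them at 20 leave (75 − 40)/3 = 11.67 for each of the others at the smallest possible spread. The SD is then √[(2 × 5² + 3 × 3.33²)/4] = 4.56. So 15 ± 3, if ± is an SD over five volunteers, cannot contain two positives. If ± is a standard error (SD = 3√5 = 6.7) it could, but section 1.3.3 still places the two at about 15%.

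**3. Test the seropositivity target against each comparator** (Fisher's exact test).

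- 10/15 v 2/5: twelve positives among 20. The probability of the observed table is C(15,10)·C(5,2)/C(20,12) = 30,030/125,970 = 0.238. Adding the tables no more probable (7, 11 and 12 positives in the FMP010 group) gives (30,030 + 6,435 + 6,825 + 455)/125,970 = **0.347**. One-sided: 0.296. Chi-square, Barnard and Boschloo tests give 0.29 or more.
- 10/15 v 0/5: ten positives among 20. 2 × C(15,10)/C(20,10) = 6,006/184,756 = **0.033**.

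Smallest counts reaching two-sided p < 0.05:

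| FMP010 group size | against 2/5 | against 0/5 |
|---|---|---|
| 15 | 14 | 9 |
| 16 | 15 | 9 |
| 20 | 18 | 11 |

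The exact 95% interval for 2/5 is 5% to 85%. If true rates were 67% and 40%, exact Fisher power would be about 12% at 15 v 5 and 15% at 20 v 5.

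**4. Check the other row of the table.** For means 30 and 15 with groups of 15 and 5:

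- ± as SD: t = 15/√(25/15 + 9/5) = 8.06, Welch p < 0.0001.
- ± as SE: t = 15/√(25 + 9) = 2.57, Welch p = 0.019; a pooled t-test gives p = 0.11.

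So the result in step 3 concerns the seropositivity row only.

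**5. Carry the target to Group 3.** Two thirds of 20 is 13.3, so at least 14; two thirds of 16 is 10.7, so at least 11. Ten of 20 is 50%.

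| True positivity | P(at least 10 of 20) | P(at least 14 of 20) |
|---|---|---|
| 40% | 24% | 0.6% |
| 50% | 59% | 6% |

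Fisher two-sided p at these counts:

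| Result | v 2/5 | v 0/5 |
|---|---|---|
| 10/20 | 1.00 | 0.061 |
| 14/20 | 0.31 | 0.009 |
| 11/16 | 0.33 | 0.012 |

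Read as a bare count at n = 20, the target is not significant against either comparator. Read as a proportion, it is significant only against 0/5.

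**The case against.** Several stronger conclusions are tempting, and the case against them is good.

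- **That the criterion cannot deliver the significance it claims.** A reader might infer this from p = 0.35. That value depends on keeping the 2/5 which the cutoff contradicts; against 0/5 the target is significant. The sentence on significant differences is also not tied to the seropositivity row, and the mean-inhibition row can reach significance. Only the conditional statement stands.
- **That 15 is an error for 20.** The criterion speaks of the vaccine's progression, not of Group 3, and the section 10 objectives cover both US and Kenyan adults. The FMP1 volunteers were malaria-naïve US adults, so the nearest comparison lies in Part A. Fifteen might be a Part A group or an evaluable subset. What stands is that the text names no group.
- **That the true FMP1 count is 0/5 and that 15 is the mean of two volunteers.** Section 1.3.3 gives no individual values or serum concentration, and section 10.4.3 does not say whom the mean covers. The documents show a conflict to be reconciled; 0/5 is what their own figures imply.
- **That only a standard-error reading of 30 ± 5 fits 67%.** Under a normal model an SD of 5 would put 98% above the cutoff, but 67% is a floor, so 98% satisfies it. The undefined ± is a small omission.
- **That fixing 40% as a known historical rate rescues the target.** It gives a one-sided exact p of 0.034 for 10/15, but ignores the 5% to 85% interval around 2/5, and the text speaks of a difference between two vaccines.

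The protocol also admits low power in its sample size section, and a statistical analysis plan may name the test. Neither removes the conflict among figures that the protocol itself states.

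**Conclusion.** The concern holds as an internal inconsistency. The comparator's 2/5 conflicts with the > 20% rule and the roughly 15% reported for those volunteers. On the seropositivity row, whether the target meets the stated basis depends on that unreconciled count: p = 0.35 against 2/5, p = 0.033 against 0/5. The denominator of 15 is tied to no named group. If the rule is applied to Group 3, its count and its percentage diverge, with pass rates of 24% and 0.6% at a true positivity of 40%.

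This rests on an assumed level of 0.05 (one-sided testing leads to the same conclusions), on the figures in section 1.3.3, and, for the pass rates, on applying the rule to all 20 of Group 3.

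It should be fixed, but is not critical. GIA is a secondary endpoint and the primary objective is safety. A reader might infer that this is the protocol's only go/no-go rule; it is not, because the protocol also governs progression from Part A to Part B and between doses. It is the only rule for Phase 2b.

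**What to change.** Amend the criterion in section 10.4.3, before unblinding:

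- Rescore the FMP1/AS02A row with the same > 20% rule, or cite the values that support 2/5. Say which volunteers the mean of 15 covers.
- Name the group to which the target applies, and state the target as a proportion of that group with an exact confidence interval. If it is Group 3, two thirds means at least 14/20, or 11/16 at the minimum size.
- For the seropositivity row, either drop the significance wording or state the test and the count that reaches it at the chosen size. At 20 v 5 with Fisher's test that is 18 against 2/5, or 11 against 0/5.
- As a minor clarification, say whether ± is SD or SE.

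The cost is wording only: no visit, sample or assay changes. The criterion may become less favourable to the vaccine.
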